**1. Title**

A clinical study to assess clinical performance and safety of a novel interface device for BIS monitoring, which was developed to use needle electrodes for patients whose clinical condition does not allow conventional BIS monitoring

**3. Background and rational of the study**

BIS monitoring quantifies consciousness-related activity of cerebral cortex based on frequency, amplitude, and interference, and is used to assess the depth of anesthesia and sedation. Intraoperative BIS monitoring enables more appropriate dosing of anesthetics and therefore is considered to reduce the risk of intraoperative arousal due to excessive sedation or too light anesthesia. In the United States of America, the use of BIS is estimated to be about 70% of general anesthesia.

BIS monitoring is usually performed with a dedicated sensor attaching to forehead to acquire frontal lobe EEG. However, if the appropriate position of the sensor is within a surgical site or an antisepticated operative field, or if controlling the sensor by anesthetist is difficult due to cervical surgery, it is often not possible to attach a dedicated sensor to an appropriate position. In

those cases the attachment position is shifted toward nasal tip. However, if the distance is increased, the reliability of BIS becomes poor, due to an increased far field potential and a lowered signal quality index (SQI) of the electroencephalogram (EEG).

In such cases, it would be of extremely great clinical significance, if the needle electrodes, which have been clinically used for many years, are placed in forehead and can be connected to the BIS monitoring device via a dedicated sensor.

We developed a device that connects commercially available needle electrodes and the BIS monitor via a commercially available dedicated sensor for BIS. Therefore, we planned this clinical study to assess the clinical performance and safety of this device.

The device is as follows:

[figure not shown]

Complete view of the newly developed interface device used between commercially available needle electrodes and the existing BIS sensor

The left part consisting of four black electrodes enables to connect to NE-220B, the needle electrodes for EEG manufactured by Nihon Koden.

The right part is the conversion device receiving a commercially available BIS sensor, and the part with silver plate electrodes is reusable silver/silver chloride plate electrodes, which enabled to get the optimal electrical resistance through a test as diagramed below.

[figure not shown]

[figure not shown]

#### 4. Aim of the study

To evaluate the clinical performance and safety of a newly developed BIS monitoring converting device using already existing needle electrodes in patients undergoing perioperative EEG monitoring as a subject.

#### 5. Study design

Prospective study

#### 6. Method of participant selection

##### 6-1. Eligible patient and method of recruitment

Those who undergo surgery under intraoperative management by total intravenous anesthesia in the Department of Neurosurgery or Plastic Surgery at Kurume University Hospital

The target number of cases: 20 patients

##### 6-2. Inclusion criteria

Patients who fulfill all of the following will be eligible:

- Patients aged 20 years or older when the consent was obtained
- Patients who provided written consent
- Patients with ASA1 or 2

##### 6-3. Exclusion criteria

Patients who fulfill any of the following will be excluded:

- Patients with injury or skin disease on the forehead
- Patients with altered levels of consciousness before surgery due to intracranial disorders
- Patients with a surgical procedure impeding BIS sensor attachment at the forehead
- Patients with a neurological disorder
- Patients with a psychiatric disorder
- Patients with pathergy test positive
- Patients with metal hypersensitivity

## 7. Study period

Study period: from June, Heisei 28 (2016) after approval by the ethic committee until December 31, Heisei 30 (2018)

## 8. Study methods

In patients undergoing regular surgery in the Departments of Surgery or Plastic Surgery, who are planned for electrophysiological monitoring and provide consent, the study will be conducted as follows:

### 8-1. Detailed procedure

The patient will be brought into the operation room with usual medical procedure, and a commercially available BIS sensor will be attached to the forehead of the patients immediately after the introduction of anesthesia needle electrodes, and the perioperative consciousness levels and association in various BIS-related values will be compared.

- I. Before the introduction of anesthesia, both needle electrodes and a commercially available BIS sensor will be attached at the same place of the forehead
- II. Anesthesia will be introduced by propofol, remifentanyl, and rocuronium
- III. Normal anesthesia management will be done
- IV. Because the needle electrodes and the commercially available BIS sensor are at the same position, there should be no difference. The BIS monitoring system used in this study can display BIS

values from two areas, and the electrodes are attached at the same position. The homology of the EEG wave form will be observed, values calculated using EEG processing, such as SQL, SEF, Beta-ratio, and resting ratio, will be compared and recorded if there is any discrepancy and if so in which degree.

- V. After completion of the surgery, it will be recorded if there is any discrepancy and if so in which degree in increasing BIS values due to emergence.

8-2. Devices to be used (All of them are medical devices approved for clinical use)

1. NE-220B, the needle electrodes for EEG manufactured by Nihon Koden (length, 13mm; diameter 0.4mm).
2. BIS™ Complete 4 Channel Monitoring System
3. BIS™ Bilateral Sensor

8-3. Methods of allocation

This study acquires and compares information from two sensor locations in a single person. Therefore, there is no allocation.

8-4. Endpoints

Primary endpoints : BIS-related values from two different measurement locations

Secondary endpoints: perioperative complications

8-5. Analysis methods

By repeated ANOVA (post hoc test) and sequential two-group comparisons of BIS-related values, it will be proven that the observed values are the same.

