## **13. Consent of patients (informed consent)**

Before perioperative period, consent will be obtained from the participants after explaining about the study. A withdrawal form will be handed out, and if the patient withdraws the consent by giving the withdrawal form or explaining verbally before the anesthesia introduction, the patient will be excluded from the study.

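### The opening sentence of section 8-1 is ambiguous and, on its most natural reading, contradicts step I on whether the BIS sensor goes on before or after induction

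*Protocol*

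**What the plan says.** Section 8-1 describes sensor attachment twice. The opening paragraph says that the commercial BIS sensor "will be attached to the forehead of the patients immediately after the introduction of anesthesia needle electrodes", and the same sentence goes on to say that "the perioperative consciousness levels and association in various BIS-related values will be compared". The numbered procedure then begins with step I: "Before the introduction of anesthesia, both needle electrodes and a commercially available BIS sensor will be attached at the same place of the forehead". Step II follows: "Anesthesia will be introduced by propofol, remifentanyl, and rocuronium". Steps III and IV cover anesthetic management and the comparison of the two channels. Step V turns to emergence: "After completion of the surgery, it will be recorded if there is any discrepancy".

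Section 8-4 makes the BIS-related values from the two measurement locations the primary endpoint and names no time points. Section 8-5 plans a repeated ANOVA with post hoc tests and sequential two-group comparisons, with the stated purpose of proving that the values are the same. Section 11-2 names subcutaneous bleeding and infection as possible effects of the needles. It does not say whether the patient is awake or anesthetized when they go in.

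**The concern.** A paired comparison exists only while both channels record. The moment at which the later of the two is attached is therefore the start of the data. If one sentence puts that moment before induction and another after it, the procedure does not give a single answer on whether the awake state and the fall into anesthesia are observed in pairs.

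This is a matter of study conduct. A statistical analysis plan can choose which time points to analyze, but it cannot supply values that were never recorded. Section 8-5 states its aim without limit of phase, so a reader of the results could take sameness to cover phases that have no paired data. The order may also bear on whether needles are inserted in an awake or an anesthetized patient, on which section 11-2 is silent.

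**Working it through.** No figure in the protocol bears on this point and no formula applies. The check is a comparison of texts.

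**1. What the protocol means by introduction.** In steps I and II, introducing anesthesia is induction. Section 13 uses the word in the same way when it allows the patient to withdraw by form or by "explaining verbally before the anesthesia introduction". Needle insertion is not called introduction elsewhere: section 3 speaks of placing the needles and step I of attaching them.

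**2. What the protocol calls the needles.** The device list in 8-2 has "NE-220B, the needle electrodes for EEG manufactured by Nihon Koden", and sections 3 and 11-2 likewise call them needle electrodes for EEG. The combination of the word anesthesia with needle electrodes, as printed in the opening sentence, occurs nowhere else. Words appear to be missing there.

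**3. The two readings of the opening sentence.**
- *Reading A:* the sensor goes on after induction, with words lost before the mention of the needles. This fits the vocabulary in points 1 and 2, and it contradicts step I.
- *Reading B:* the sensor goes on after the needles have been inserted. This takes the printed words literally and gives only an order of devices. It agrees with step I.

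**4. What each order allows.** The four phases below are a division made here from the sequence of steps I to V; the protocol does not define them. The entries are the number of patients, out of the target of 20 in section 6-1, who could contribute paired values.

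| Phase | Step I, or reading B | Reading A |
|---|---|---|
| Before induction | up to 20 | 0 |
| Induction | up to 20 | 0 |
| Maintenance | up to 20 | up to 20 |
| Emergence | up to 20 | up to 20 |

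Reading A removes two of the four phases and leaves the other two untouched. This holds even if only the sensor is late and the needles are already in place, because one missing channel is enough to remove the pair. When the needles themselves go in under reading A depends on how the missing words are restored, and the text does not settle that.

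**5. What the comparison needs.** The opening sentence promises a comparison over perioperative consciousness levels. Under reading A the change of level would be seen in pairs in one direction only, the rise at emergence in step V. Under step I the fall at induction can be seen as well.

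**The case against.** The strongest reply is that there is no definite conflict. As printed, the opening sentence has the needle electrodes as its object, so it can be taken as needles first and sensor second, and that fits step I. The numbered steps are explicit and in order, and the opening paragraph is only a summary of them. This stands in part: it rules out calling the sentence a certain contradiction. It does not remove the defect, because the protocol's own vocabulary favors the reading that opposes step I.

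A second reply is that no endpoint or analysis names an awake baseline or an induction time point, and that emergence is compared whatever the attachment time. Both statements are correct, and they confine the consequence to two phases.

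A third reply is that time points and tables by phase are commonly left to a statistical analysis plan, which is not shown. That is fair for details such as a formal time zero, and none is asked for here. It does not cover the attachment order, nor the unrestricted aim that section 8-5 itself states.

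A fourth reply is that section 11-2 would be silent on the patient's state at insertion under step I alone. That is also true, so the ambiguity did not create that gap. Section 11-2 should simply agree with whatever order results.

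**Conclusion.** The point holds as an ambiguity that amounts to a contradiction on the most natural reading. Its size is the presence or absence of paired values before and during induction, from up to 20 patients or from none. Maintenance and emergence are not affected. The conclusion rests on reading the opening sentence in the light of the protocol's other uses of introduction; a literal reading agrees with step I.

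Three stronger conclusions might be inferred, and the documents do not support them. One is that it is wholly undetermined whether awake values will be recorded: step I is explicit and step II follows it. Another is that different teams will follow different sentences, so that patients start at different phases: the protocol describes 20 patients at one hospital and no such division of work. The third is a numerical loss of BIS range: the protocol gives no BIS values for the awake or anesthetized state, and emergence is paired either way.

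Which attachment order is right is a clinical matter that this review does not decide.

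**What to change.** - **Section 8-1:** reconcile the opening sentence with step I so that one attachment order, for needles and sensor alike, applies to all 20 patients.
- **Section 11-2:** make the description of risks and disadvantages consistent with that order.
- **Section 8-5:** report bias and limits of agreement between the two channels by phase (before induction and induction if paired, maintenance, emergence), by a method that allows for repeated readings within a patient. Limit the claim of sameness to the phases in which both channels were recorded. This addresses sameness more directly than repeated ANOVA alone, where the absence of a significant difference does not show agreement.

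The cost is a one-sentence correction in 8-1, a consistency check in 11-2 and one table. No added patients or measurements are needed. The small downside is that any phase without paired data drops out of the claim.

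### The protocol takes zero as the needle-versus-sensor difference and plans to prove sameness, but has no reference for the conventional sensor's own variability and contradicts itself on whether the two pick-ups share a position

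*Protocol*

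**What the plan says.** All the relevant text is in section 8 of the Protocol.

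- **Placement (8-1, step I):** "both needle electrodes and a commercially available BIS sensor will be attached at the same place of the forehead".
- **Expected result (8-1, step IV):** "Because the needle electrodes and the commercially available BIS sensor are at the same position, there should be no difference". The EEG-derived values "will be compared and recorded if there is any discrepancy and if so in which degree".
- **Allocation (8-3):** "This study acquires and compares information from two sensor locations in a single person. Therefore, there is no allocation".
- **Primary endpoint (8-4):** "Primary endpoints : BIS-related values from two different measurement locations".
- **Analysis (8-5):** by repeated ANOVA and sequential two-group comparisons, "it will be proven that the observed values are the same".

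The comparison described is needle electrodes against the commercial sensor. No period, patient or channel is described in which two conventional pick-ups are compared, and no repeatability figure for the conventional sensor is given. Section 6-1 sets 20 patients without a derivation. The protocol states no acceptable difference.

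**The concern.** Disagreement between two measuring systems contains the error of both. A BIS value is a processed estimate, so two conventional sensors would be expected to disagree to some degree too. Step IV sets that degree at zero by argument rather than by measurement. Once a spread is observed, the protocol offers nothing to show how much comes from the needle interface and how much from the comparator.

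The argument for zero rests on a shared position, and sections 8-3 and 8-4 contradict it. This matters on the protocol's own account: section 3 says that BIS becomes less reliable as the sensor moves away from its proper site. If the locations differ, and position or channel is not balanced between the two systems, a location effect is mixed with any device effect.

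The tests in 8-5 do not rescue the comparison. They address means, so two channels with equal averages and poor reading-by-reading agreement would pass. Failure to reject is not evidence of sameness, and noisier data make it more likely. The performance half of the study aim (section 4) is at stake.

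**Working it through.** **The plan's own figure.** The target of 20 cannot be reproduced, because the protocol gives no alpha, power, SD, difference or margin. What follows is illustration. From the document: n = 20, taken as one paired difference per patient. Every SD below is an assumption.

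**1. How far two sound conventional channels might differ.** Let σ be the error SD per channel and ρ the correlation of the errors. The SD of a difference is σ√(2(1−ρ)), and the 95% limits are ±1.96 times that.

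| Assumed σ (BIS points) | SD, ρ = 0 | Limits, ρ = 0 | SD, ρ = 0.5 | Limits, ρ = 0.5 |
|---|---|---|---|---|
| 2 | 2.83 | ±5.5 | 2.0 | ±3.9 |
| 4 | 5.66 | ±11.1 | 4.0 | ±7.8 |
| 6 | 8.49 | ±16.6 | 6.0 | ±11.8 |

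Under independence, an observed needle-versus-sensor result of ±11 would be twice the ordinary spread in the first row and well inside it in the last. Correlated errors shrink the limits but leave the threefold range.

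**2. How much of an observed spread is the device.** Assume a needle-versus-conventional SD of 8 (limits ±1.96 × 8 = ±15.7). With S_cc the unmeasured conventional-versus-conventional SD, the variance added by the needle path is 8² − S_cc², and its share is 1 − S_cc²/64.

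| S_cc | Share added by needle path |
|---|---|
| 0 | 100% |
| 4 | 48/64 = 75% |
| 6 | 28/64 = 44% |
| 8 | 0% |

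**3. What the 8-5 tests can show with n = 20.** A paired t-test has about 56% power for a true shift of 0.5 SD, so it misses such a shift about 44% of the time. Power reaches 80% only at 0.66 SD.

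**4. What estimation can show with n = 20.**
- Mean difference: 95% CI half-width t(0.975, 19)/√20 = 0.47 SD.
- Each limit of agreement: half-width t × √(1/20 + 1.96²/(2 × 19)) = 0.81 SD.
- SD of differences: 95% CI from 0.76 to 1.46 times the estimate.
- Ratio of two SDs on 19 and 19 df, treated as independent: 95% CI from 0.63 to 1.59 times the estimate.

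At an SD of 8 these give about ±3.7 points for the mean difference (0.47 × 8 = 3.76; 3.74 unrounded) and ±6.5 for each limit (0.81 × 8). Several epochs per patient would add information on within-patient SDs, by an amount that depends on serial correlation.

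**5. What drift does to a repeatability ratio.** If true drift with SD δ enters both channels, the ratio becomes √((σn² + δ²)/(σc² + δ²)). With assumed σn = 6 and σc = 4 the true ratio is 1.5. With δ = 4 it reads √(52/32) = 1.27. Shared drift pulls the ratio towards 1.

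**The case against.** A reader might infer that without a conventional-versus-conventional reference no observed difference can be attributed to the device or cleared. The documents do not support that. A prespecified acceptable limit could clear a mean difference without any such reference: with 20 patients, two one-sided tests at a margin of 0.66 SD have about 77% power when the true difference is zero. The protocol states no limit, but a statistical analysis plan, not available here, might. A gross or trivial difference would also be interpretable as it stands.

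A reader might also infer that every discrepancy counts against the interface. Step IV does not say so. It has discrepancies recorded and graded, and it compares EEG waveforms and other processed values, which could help to explain them. Nor does section 3 show that two pick-ups at one position must disagree; it concerns displacement of the sensor.

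It is tempting to call for a control window with two conventional inputs, since 8-2 lists a "BIS™ Bilateral Sensor" and step IV describes a two-area display. The documents do not show that this equipment can give a conventional pair at one position. A left-right pair would add a location difference, and reconnecting leads during surgery is an extra procedure.

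Finally, the repeatability estimate proposed below uses data already being recorded, so part of the gap is one of analysis. That stands, and it is why the fix is cheap. It does not excuse 8-5, which itself names an analysis that cannot show sameness.

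**Conclusion.** The point holds in limited form. The protocol assumes zero difference, promises to prove sameness, and gives no reference for the comparator's own variability. It therefore cannot separate device-related spread from ordinary noise, and the tests it names cannot establish agreement. It also contradicts itself on whether the pick-ups share a position, and those passages must be reconciled.

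The size cannot be fixed from the documents, because no SD is given. On the assumed values, one observed spread is compatible with anything from no device contribution to all of it. That conclusion does not depend on a particular SD, and error correlation changes the limits but not the ambiguity. The precision figures assume one approximately normal paired difference per patient and, for the SD ratio, independent comparisons. This is a worthwhile and inexpensive correction to the primary comparison. It does not make the study uninterpretable.

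**What to change.** 1. **8-1, step IV:** delete the statement that there should be no difference as a premise.
2. **8-1, 8-3 and 8-4:** reconcile the statements on one position and two locations.
3. **8-5:** replace the proof of sameness by ANOVA and two-group tests with, for example: *Agreement will be described by the mean needle-minus-conventional difference, the SD of differences and the 95% limits of agreement, each with a confidence interval, allowing for repeated readings within patient.*
4. **8-5, add:** *Each channel's within-patient repeatability will be estimated from successive epochs of stable maintenance in the simultaneous recordings. Needle-versus-conventional disagreement, and the ratio of needle to conventional repeatability with its confidence interval, will be reported against it.* Define stable epochs in advance. The within-patient part of the disagreement is the like-for-like comparison.

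**Costs and limits.** The change needs some extra analysis and no extra patients or recording. Repeatability includes true drift, which inflates the benchmark and pulls the ratio towards 1. It does not capture fixed offsets between sensors, so the mean difference must be read separately. Precision with 20 patients is modest.

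A conventional-versus-conventional control window is optional, and only if the hardware can supply one at the same position without an extra intraoperative procedure.

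### If few of the 20 patients show suppression, the tests in 8-5 could pass the resting ratio as the same even though the needle channel missed every episode

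*Protocol*

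**What the plan says.** Both channels are read in the same patient (8-3): "This study acquires and compares information from two sensor locations in a single person". The sample size in 6-1 is given without any supporting calculation: "The target number of cases: 20 patients".

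Step IV of 8-1 names the resting ratio as one of several derived readings to be set side by side: "values calculated using EEG processing, such as SQL, SEF, Beta-ratio, and resting ratio, will be compared and recorded". The sentence goes on to ask that any divergence and its size be noted, and the same step has the two EEG traces watched for similarity.

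Section 8-4 makes the whole family of readings primary: "Primary endpoints : BIS-related values from two different measurement locations". Section 8-5 states one analysis and one conclusion for that family: "By repeated ANOVA (post hoc test) and sequential two-group comparisons of BIS-related values, it will be proven that the observed values are the same".

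The protocol does not define the resting ratio, give an expected frequency of non-zero values, set a margin or agreement limit, or name the unit of analysis (patient, time point or single reading).

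**The concern.** The resting ratio is read here as the suppression ratio, the share of flat EEG. On that reading it is zero unless suppression occurs, and only patients who show suppression tell us whether the needle channel picks it up. A comparison of averages over all 20 patients then rests on however many such patients there happen to be. If there are few, a non-significant result is close to guaranteed, and 8-5 would read it as proof that the channels match.

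Section 4 sets out to evaluate clinical performance, and section 3 mentions excessive sedation among the reasons for BIS monitoring. A statement that the resting ratio is the same on both channels would suggest that the needle channel shows suppression when the standard sensor does. The tests may be unable to support that.

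This differs from the general weakness that a non-significant difference does not prove sameness. The usual repair for that weakness, an equivalence margin or limits of agreement on the mean difference, could also pass a complete miss on this value, as shown in the working.

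**Working it through.** **Inputs.** n = 20 patients (6-1); paired readings within patient (8-3); tests as in 8-5. The plan gives no alpha, power, SD or margin, so there is no figure of its own to reproduce. Assumed: two-sided 0.05, so the critical t on 19 df is 2.093.

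**Worst case.** The needle channel reads zero throughout. The standard sensor is above zero in k patients and both channels are exactly zero in the other 20 − k. The protocol gives no value for k, so a range is shown.

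**Step 1: largest possible patient-level t.** Let the patient mean differences have sum S and sum of squares Q. Then t² = (n − 1)/(nQ/S² − 1). With k non-zero differences, Q/S² is at least 1/k, reached when all k are equal. Hence the largest t is √[k(n − 1)/(n − k)] = √[19k/(20 − k)], whatever the depth or duration of suppression. The device main effect of a two-device repeated-measures ANOVA, tested on patient means, is the same test.

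| k | largest t | smallest p (19 df) |
|---|---|---|
| 1 | √(19/19) = 1.00 | 0.33 |
| 2 | √(38/18) = 1.45 | 0.16 |
| 3 | √(57/17) = 1.83 | 0.083 |
| 4 | √(76/16) = 2.18 | 0.042 |
| 6 | √(114/14) = 2.85 | 0.010 |

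With k ≤ 3 the test cannot reach p<0.05. An exact signed-rank test has smallest p = 2 × 0.5^k, that is 0.0625 at k = 5 and 0.031 at k = 6, so it needs k ≥ 6.

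**Step 2: unequal amounts missed.** The table is the best case. With lognormal patient burdens (log-SD 1, assumed), the simulated chance that the paired t reaches p<0.05 is 4% at k = 4, 29% at k = 5, 50% at k = 6, 77% at k = 8 and 89% at k = 10.

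**Step 3: time points and pooled readings.** Assumed: 60 time points, one five-reading episode per suppressing patient, lognormal depth with median 15, 500 runs.

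- Device main effect: 0% at k ≤ 3, 64% to 67% at k = 4, 100% from k = 6. Burdens are more even here than in step 2.
- Time-point tests, episodes scattered: at least one unadjusted p<0.05 in 0% of runs at k ≤ 4, 0.8% at k = 6 and 7.6% at k = 10. After Bonferroni, 0% up to k = 15.
- Time-point tests, episodes clustered at induction: unadjusted 0% at k ≤ 3, 21% at k = 4, 94% at k = 6. After Bonferroni, 0% at k ≤ 8, 1.4% at k = 10, 91% at k = 15.
- All readings pooled as independent: about 65% at k = 1 and nearly 100% from k = 2. This ignores clustering within patients.

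**Step 4: would the usual repair catch it?** Take k = 2 with 10 points missed in each.

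- Mean difference = 2 × 10/20 = 1.0.
- SD = 10 × √(0.1 × 0.9 × 20/19) = 3.08.
- Limits of agreement = 1.0 ± 1.96 × 3.08 = −5.0 to +7.0.
- 90% confidence interval = 1.0 ± 1.729 × 3.08/√20, about −0.2 to 2.2.

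An equivalence margin above about 2.2 points would be met, yet agreement on readings above zero is 0%, because the two channels are never above zero together.

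**The case against.** The strongest reply is that step IV already catches the failure. The traces are watched side by side, and the plan asks that it be "recorded if there is any discrepancy and if so in which degree". A needle channel at zero through an episode is such a discrepancy, so a miss could well be noted. That stands, and the plan should get credit for it. But 8-5 draws the conclusion from the tests and gives the record no role in it.

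Second, the outcome depends on unknowns. The protocol names the drugs ("Anesthesia will be introduced by propofol, remifentanyl, and rocuronium") but not how often suppression is expected. With many suppressing patients the device main effect usually finds a complete miss, and pooled readings find it sooner. This also stands. A reader might infer that the plan would always call the channels the same; the documents do not support that.

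Third, a reader might infer that the sheer number of readings at zero on both channels decides the result. It does not. At k = 10 in step 3, 1 − 50/1,200, or about 96%, of readings are zero on both channels, and the device main effect still detected the miss in every run. What decides is the number of suppressing patients and the unit of analysis.

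Fourth, the two-group comparisons might be rank-based, and the choice of test can be left to a statistical analysis plan that is not shown. That is fair, but a signed-rank test needs even more suppressing patients, and the protocol itself already fixes the tests as the proof of sameness.

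Fifth, this overlaps with the general fault of reading non-significance as sameness. In part it does. The separate part is step 4: repairing only the general fault could leave this value wrongly passed.

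**Conclusion.** The point holds in conditional form. The tests in 8-5 could declare the resting ratio the same although the needle channel missed every episode, when few of the 20 patients show suppression. For a patient-level test this is certain at three or fewer such patients. At four to six, detection is unreliable (4% to 50% with unequal burdens). At about ten or more the miss is usually found (89%). Time-point tests stay weak for longer if episodes are scattered.

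This rests on two assumptions that the protocol neither confirms nor excludes: that the resting ratio is the suppression ratio, and that it is zero in most patients. It also rests on the worst case of a complete miss and on exact zeros in the remaining patients.

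Two further inferences are not supported. Nothing in the protocol suggests that the needle channel does miss suppression. Nor does it say that detecting suppression is the sole purpose of this value. One listed component of the primary endpoint is affected, not the whole comparison.

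**What to change.** In 8-5, do not base the conclusion for the resting ratio on the ANOVA or the two-group tests. Instead:

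- Define the resting ratio and state the unit of analysis.
- Report the number of patients and of epochs with a value above zero on either channel.
- Report positive and negative agreement on being above zero, with intervals that allow for clustering of epochs within patients.
- Report the size of the difference only in epochs where at least one channel is above zero.
- Judge these results against a limit set before the data are seen, and state that epochs at zero on both channels do not count as evidence that the needle channel detects suppression.
- Set in advance a minimum number of patients with suppression. Below it, conclude that this value was not assessable.
- Give the discrepancies recorded under step IV a stated place in that conclusion.

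The cost is a wording change and one extra table from readings the plan already collects, with no added patients or measurements. The downside is that the result for this one value may be not assessable.
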